Systems biology, defined as multiple comics integration and consolidation from genes, cells, the organization of individuals, is the TCM pattern efficacy and mechanism research method fitting with TCM theory, characteristics and discipline [11–13]. Hence, we utilize high throughput screening (HTS) technology of systems biology; that is transcriptomics, metabonomics, proteomics, and so on, to promote fundamental research of TCM pattern, global Chinese compound medicine selection, evaluation and technology platform. In recent years, a comprehensive approach has shown the TCM efficacy mechanism of SAP in the view of regulating lipid metabolism abnormality and resisting inflammatory expression and endothelial dysfunction [14]. However, there is not adequate understanding of the interaction and relationship between spleen deficiency generating phlegm of SAP (response system) and regulation from spleen (intervention system) through the scattered and small-scale reduction biological research. Notably, we should explore the clinical evaluation and efficacy mechanism and regulation on the foundation of systems biology and evidence-based medicine (EBM).

In this trial, we intend to investigate the efficacy mechanism for SAP with spleen deficiency and phlegm pattern through brain-gut axis regulation of lipid metabolism, immune inflammation and vascular endothelial network. Meanwhile, we attempt to further validate the effectiveness and safety in light of clinical efficacy evaluation index, which is the frequency and duration of angina pectoris attacks, health-related quality of life, and so on.

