### Outcomes

#### Efficacy outcomes

The primary outcomes include:Frequency of angina pectoris attacksDosage of nitroglycerinBody limited dimension of Seattle Angina Questionnaire (SAQ)

The secondary outcomes include:SAQ except for the body limited dimensionTCM pattern questionnaireThe duration of angina pectorisAngina pain severity

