#### Therapeutic mechanism outcomes

Blood serum metabolites; total cholesterol (TC); triglycerides (TG); low-density lipoprotein (LDL); high-density lipoprotein (HDL); ox-LDL; hypersensitive C reactive protein; homocysteine; glucagon like peptide-1; angiotonin II; HMG-COA reductase; adherence factor PS; scavenger receptor A; scavenger receptor B; chemokine MCP-1; adherence factor vascular cell adhesion protein (VCAM)-1; 5-HT; vasointestinal peptide (VIP); ghrelin; norepinephrine (NE); acetylcholine (Ach); mtDNA copy number; MicroRNA155; MicroRNA 33; MicroRNA 126; MicroRNA 125; MicroRNA 221; MicroRNA 222.

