### Statistical analysis

The statistical analysis will be conducted by a statistician of the Beijing Bozhiyin Science and Technology Co. Ltd, China. They are blinded to the whole trial and using Statistical Analysis System (SAS, Cary, NC, USA) version 9.2 and Statistic Package for Social Science (SPSS, Chicago, IL, USA) version 17.0 software packages. All mechanism, efficacy and safety analyses will be strictly conducted according to the intention-to-treat (ITT) principle and the full analysis set (FAS) population, the per-protocol set (PPS) population and the safety set (SS) population. Missing values will be replaced by the last observation carried forward (LOCF) method.

The statistical significance is defined as a two-sided *P*-value of <0.05 and 95% confidence interval. For descriptive statistics, continuous variables will be described as numerous, mean ± standard deviation, median, Q1 to Q3 and mini-maxi and dichotomous data will be reported as frequency and percentage. Baseline differences among the groups will be assessed with the use of Student’s *t*-test for normally distributed continuous variables and the non-parametric Mann-Whitney *U*-test for non-normally distributed variables. Comparisons between groups will be conducted by using an analysis of covariance (ANCOVA) with baseline as covariate. For efficacy analysis, changes from baseline to endpoint of treatment in scores will be tested with repeated measure analysis of variance (ANOVA). Within group differences will be assessed with paired *t*-test for normally distributed data and Wilcoxon signed-rank test for non-normally distributed data. Mechanism will be assessed between mechanism index and primary outcomes by ANCOVA and regression analysis. Safety will be assessed by participant compliance and adverse events. The endpoint events will be listed by detailed account.

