## Discussion

SAP is a major public health problem, which can endanger a patient’s life quality. Currently, TCM has a considerable role in the symptom and quality of life improvement of SAP patients in China and worldwide.

Our research team has conducted a deep study of the pathogenesis, TCM pattern feature and efficacy evaluation of TCM in SAP. We proposed that the key pathogenic mechanism was phlegm and blood stasis integration owing to spleen deficiency generating phlegm and phlegm leading to blood stasis [20]. Otherwise, we have developed pattern differentiation standard of SAP and TCM pattern diagnosis and efficacy evaluation scale for pattern of phlegm and blood stasis integration [21, 22].

To our knowledge, this may be the first trial to utilize high-quality EBM evidence to assess the effectiveness and safety of SAP via TCM pattern differentiation, as well as exploring the efficacy mechanism and regulation with the molecular biology and systems biology. In the present study, we establish two treatment groups and one control group in this trial. Our aim of establishing these three groups is to differentiate and isolate the placebo effect and research bias; in particular, to further appropriately validate the accumulation effect of activating blood and removing stasis on the basis of tonifying spleen and eliminating phlegm. It is worth mentioning that we tried to contact the central regulation with the effect organ through multiple communication pathways, such as brain-gut axis regulation of lipid metabolism, immune inflammation, and vascular endothelial network, so as to explain the specific process of the efficacy mechanism and regulation of SAP from spleen.

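### The mechanism assessment is an index–outcome association that is not tied to the randomised comparison of the index, so a purely prognostic marker can satisfy it.

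*Protocol article*

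**What the plan says.** All of this is in the protocol article.

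- **Mechanism sentence (Statistical analysis).** "Mechanism will be assessed between mechanism index and primary outcomes by ANCOVA and regression analysis". The two quantities to be related are the index and the primary outcome. The sentence does not ask whether the index differs between arms.
- **General comparison (Statistical analysis).** "Comparisons between groups will be conducted by using an analysis of covariance (ANCOVA) with baseline as covariate". This is not restricted to efficacy outcomes, so it can be read as covering the indices. The same section adds: "All mechanism, efficacy and safety analyses will be strictly conducted according to the intention-to-treat (ITT) principle".
- **Indices (Therapeutic mechanism outcomes).** The list opens with "Blood serum metabolites; total cholesterol (TC); triglycerides (TG); low-density lipoprotein (LDL" and continues through inflammatory, endothelial and gut–brain markers, mitochondrial DNA copy number and microRNAs: 27 single indices besides the serum metabolites. There are three primary outcomes.
- **Aim.** The Background states: "we intend to investigate the efficacy mechanism for SAP with spleen deficiency and phlegm pattern through brain-gut axis regulation of lipid metabolism", and goes on to inflammation and endothelium. The Discussion says that these pathways are studied "so as to explain the specific process of the efficacy mechanism and regulation of SAP from spleen".

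**The concern.** The aim is causal: by what route do the granules act? An index can be such a route only if the granules move it. An association between index and outcome can arise for another reason, namely that the index marks disease severity in all patients, the control arm included. Lipids, C-reactive protein and adhesion molecules are obvious candidates for that kind of relation. The stated assessment cannot separate a severity marker from a mediator.

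The trial does hold the information to make part of that distinction, because the indices are measured in randomised arms. The effect of arm on the index is the one part of the mechanism question that randomisation protects. The plan may well produce that comparison, but the mechanism assessment is not tied to it. At stake is whether ordinary prognostic markers could be reported as ways in which the herbs work.

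**Working it through.** **Inputs from the protocol article.** 240 patients allocated 1:1:1, 80 per arm; 15% dropout; two-sided 0.05; 27 single indices; three primary outcomes.

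**The plan's own sample size.** No stated figure concerns mechanism, but the numbers used below rest on the sample size, so it was checked first. Pooled two-proportion formula without continuity correction, 80% power: n = [1.96√(2p̄q̄) + 0.842√(p₁q₁ + p₂q₂)]² / (p₁ − p₂)².

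- 88.5% v 60%: 36 per group (stated 37; power at 37 is 81.4%).
- 82.5% v 60%: 63 per group (stated 64; power at 64 is 81.1%).
- 64/(1 − 0.15) = 75.3, so 76; the planned 80 covers it.

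The figures reproduce to within one patient. Evaluable patients: 80 × 0.85 = 68 per arm, 204 in total.

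**Step 1: an index with no treatment effect but a true correlation r with the outcome.** The chance of P<0.05 in a simple index–outcome analysis is approximately Φ(√(n − 3) × atanh(r) − 1.96), with √201 = 14.18.

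- r = 0.10: 14.18 × 0.100 − 1.96 = −0.54, 30%
- r = 0.15: 14.18 × 0.151 − 1.96 = 0.18, 57%
- r = 0.20: 14.18 × 0.203 − 1.96 = 0.91, 82%
- r = 0.30: 14.18 × 0.310 − 1.96 = 2.43, 99%

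If all 240 are kept by carrying the last value forward, √237 = 15.39. The results are then about 88% at r = 0.20 (15.39 × 0.203 − 1.96 = 1.16) and over 99% at r = 0.30 (15.39 × 0.310 − 1.96 = 2.81).

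**Step 2: simulation.** 4,000 runs per setting, three arms of 68. The index is unaffected by arm and has within-arm correlation ρ with the outcome; both herb arms have an assumed 0.5 SD effect on the outcome. Percentage of runs significant at 0.05:

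| ρ | outcome on index | outcome on arm + index | index differs by arm (F test) | last two both |
|---|---|---|---|---|
| 0.1 | 27% | 29% | 5% | 1.5% |
| 0.2 | 80% | 82% | 5% | 4% |
| 0.3 | 99% | 99% | 5% | 5% |
| 0.4 | 100% | 100% | 5% | 5% |

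The second column agrees with Step 1. The third shows that putting arm in the index–outcome model does nothing to stop a prognostic index. The last shows that requiring an arm effect on the index does.

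**Step 3: why the gate itself needs error control.** The simulated gate is one three-arm F test per index. Tested formula by formula, there are 27 × 2 = 54 contrasts, and 54 × 0.05 = 2.7 would pass by chance if none were real, before any serum metabolites are counted. Hence the false discovery rate control in the fix.

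**The case against.** The strongest reply is that the randomised comparison is already in the plan. The between-group sentence is general, the indices are listed as trial outcomes, and mechanism analyses are placed under intention to treat. That stands: a reader might infer that the plan looks only at index–outcome associations, and the text does not support that.

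A reader might also infer that treatment arm is left out of the index–outcome model. The sentence names ANCOVA, which may well carry arm as its factor; the text neither includes nor excludes it. In any case Step 2 shows that arm in the model would not cure the problem.

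A third tempting inference is that severity markers would be declared the herbs' mechanism. No rule for declaring a mechanism is written, the abstract and Discussion also describe this work as exploration, and the indices are neither primary nor secondary outcomes. The point is that such a marker can satisfy the stated test, not that a false claim must follow.

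Finally, a journal article leaves modelling detail to fuller documents. That would answer a complaint that mediation models are undescribed. It does not answer this one: the article does state how mechanism will be assessed, and what it states is not the contrast that the aim needs. The 80% and 99% figures are the power to detect an assumed real correlation. They show how easily a prognostic marker passes, and are not an error rate of any written rule.

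**Conclusion.** The point holds as a matter of an ill-matched contrast, and it should be changed. The stated mechanism assessment relates index to outcome and is not tied to the comparison of the index between arms. An index that the granules never change would satisfy it in about 80% to 99% of trials at correlations of 0.2 to 0.3 with 204 patients, and in about 27% to 30% at 0.1. Requiring an arm effect on the index as well brings this to about 5% or less.

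The correlations and the 0.5 SD outcome effect are assumptions, since the article gives neither. The simulation uses a single index measurement with normal errors and an unadjusted F test on the index. The conclusion does not depend on those details, only on some indices being prognostic. The consequence is confined to mechanism claims; the efficacy comparison is untouched.

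**What to change.** Replace the mechanism sentence with three steps.

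1. For each herb arm separately against control, compare each index by ANCOVA adjusted for its baseline, at the planned end-of-treatment sampling, with false discovery rate control across the comparisons. Treat an index as a candidate mechanism for that formula only if it differs. Working arm by arm matters: the two formulas differ and the Discussion seeks the added effect of the second, so requiring both arms to differ from control would exclude formula-specific mechanisms.
2. For candidates only, relate the index to each primary outcome in a model with treatment arm, baseline index and baseline outcome. Report the result as exploratory mediation. The index is not randomised, so its relation to the outcome stays open to confounding.
3. Label an index–outcome association without an arm effect on the index as prognostic, not as mechanism.

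The cost is a change of plan wording and a few more models on data already being collected. The downside is that fewer indices can be reported as mechanism.

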### Ethics issue and informed consent

This trial is in accordance with the principles of the Declaration of Helsinki (version Edinburgh 2000). The study protocol was reviewed and approved by IRB of the Affiliated Hospital of Liaoning University of TCM (Number 2013CS (KT)-002-01), IRB of the Liaoning Institute of Chinese Medicine (Number 20130509-1), IRB of the Affiliated Hospital of Inner Mongolia National University, IRB of the Shen-Zhou Hospital of Shenyang Medical College, IRB of the First Affiliated Hospital of China Medical University and IRB of the Sheng-Jing Hospital of China Medical University. Before randomization, all eligible patients are informed of the details of the study and all the benefits and risk that they may take from this trial. Meanwhile, we require all patients to sign the written informed consent prior to enrollment, and they are given enough time to decide whether they will take part in this trial.

## Discussion

SAP is a major public health problem, which can endanger a patient’s life quality. Currently, TCM has a considerable role in the symptom and quality of life improvement of SAP patients in China and worldwide.

Our research team has conducted a deep study of the pathogenesis, TCM pattern feature and efficacy evaluation of TCM in SAP. We proposed that the key pathogenic mechanism was phlegm and blood stasis integration owing to spleen deficiency generating phlegm and phlegm leading to blood stasis [20]. Otherwise, we have developed pattern differentiation standard of SAP and TCM pattern diagnosis and efficacy evaluation scale for pattern of phlegm and blood stasis integration [21, 22].

To our knowledge, this may be the first trial to utilize high-quality EBM evidence to assess the effectiveness and safety of SAP via TCM pattern differentiation, as well as exploring the efficacy mechanism and regulation with the molecular biology and systems biology. In the present study, we establish two treatment groups and one control group in this trial. Our aim of establishing these three groups is to differentiate and isolate the placebo effect and research bias; in particular, to further appropriately validate the accumulation effect of activating blood and removing stasis on the basis of tonifying spleen and eliminating phlegm. It is worth mentioning that we tried to contact the central regulation with the effect organ through multiple communication pathways, such as brain-gut axis regulation of lipid metabolism, immune inflammation, and vascular endothelial network, so as to explain the specific process of the efficacy mechanism and regulation of SAP from spleen.

We have presented the design and protocol for a randomized controlled trial of patients with SAP together with spleen deficiency and phlegm pattern. The clinical trial protocol plays a vital role of study conduct, reporting, and appraisal. To facilitate appropriate high quality methodology and strict quality control, this protocol has been developed according to the CONSORT statement, SPIRIT 2013, and SPIRIT 2013 explanation and elaboration [23]. We particularly described our method of recruitment, randomization and allocation concealment, and data collection. In addition, we reported the TCM intervention according to Recommendations for Reporting Randomized Controlled Trials of Herbal Interventions, including dosage, action, batch number, and quantitative description. Completion of this trial may highlight evidence on the effectiveness and safety of TCM and provide the approaches on the efficacy mechanism and regulation of TCM pattern. The results of this study may generate scientific and rigorous evidence for the study of SAP via TCM pattern differentiation.

## Trial status

At the time of manuscript submission, patient recruitment for the trial is on-going.

## Abbreviations

Ach: acetylcholine
ALT: alanine transaminase
ANCOVA: analysis of covariance
ANOVA: analysis of variance
AST: aspartate aminotransferase
BBs: β blockers
BUN: blood urea and nitrogen
CCBs: calcium channel blockers
CCS: Canadian Cardiovascular Society
CHD: coronary heart disease
CONSORT: Consolidated Standards of Reporting Trials
Cr: creatinine
CRFs: Case Report Forms
CT: computed tomography
EBM: evidence-based medicine
ECG: electrocardiograph
FAS: full analysis set
GERD: gastric and esophageal reflux disease
GMP: Good Manufactory Practice
Group 1: *Yi-Qi-Jian-Pi* and *Qu-Tan-Hua-Zhuo* group
Group 2: *Yi-Qi-Jian-Pi* and *Qu-Tan-Hua-Yu* group
HCM: hypertrophic cardiomyopathy
HDL: high-density lipoprotein
HTS: high throughput screening
IRB: Institutional Review Board
ITT: intention-to-treat
LAD: left anterior descending
LCX: left circumflex
LDL: low-density lipoprotein
LM: left main stem
LOCF: last observation carried forward
NE: norepinephrine
PPS: per-protocol set
RCA: right coronary artery
SAP: stable angina pectoris
SAQ: Seattle Angina Questionnaire
SAS: Statistical Analysis System
SOP: standard operating procedures
SPSS: Statistic Package for Social Science
SS: safety set
TC: total cholesterol
TCM: traditional Chinese medicine
TG: triglycerides
UAP: unstable angina pectoris
VCAM-1: vascular cell adhesion protein-1
VIP: vasointestinal peptide
WHO: World Health Organization
WM: western medicine.
